**Statistical Methods, Sample Size Considerations and Statistical Analyses:**

The phase 1 of SGI-110 in combination with ipilimumab is designed as a dose-escalation study. The primary end-point will be the, Maximum Tolerated Dose (MTD) and safety of the combination of SGI-110 plus ipilimumab.

Six patients will be treated at the first dose level for one cycle.

In the absence of dose-limiting toxicities (DLTs), the starting dose of SGI-110 of 30 mg/m^2 day (Dose Level 0) will be escalated to 45 mg/m^2 day (Dose Level +1) on Days 1-5. In the absence of DLT in Dose Level +1, the dose of SGI-110 of 45 mg/m^2 day (Dose Level +1) will be escalated to 60 mg/m^2 day (Dose Level +2) ) on Days 1-5 (Level +2). In the presence of 1 DLT in 3 subjects of the single dose cohort, the cohort will enroll 3 more subjects at the same dose level. In the event that 2 or more DLTs were encountered at the single dose cohort, the previous lower dose level will be evaluated. The MTD will be the highest SGI-110 Dose Level (15-60 mg/m^2 day on Days 1-5) in combination with ipilimumab at which no more than 1 of 6 patients experiences a DLT. Once the MTD is established, additional subjects will be treated at that dose up to a total of 19 subjects in the study. If no irDCR is observed the study may be terminated.

DLT is defined as any of the following events occurring during the first treatment cycle and clearly related to study treatment: grade 4 neutropenia (absolute granulocyte count  $< 0.5 \times 10^9 /L$ ,  $\geq 5$  days), febrile neutropenia grade  $\geq 3$  (absolute granulocyte count  $< 1.0 \times 10^9 /L$  and fever  $\geq 38.5^\circ C$ ), platelet count  $< 25.000/L$  or thrombocytopenic bleeding, AST or ALT grade  $\geq 3$  for 7 days, any grade 3 or 4 non-hematologic toxicity (excluding alopecia, non pre-medicated nausea and vomiting), grade 3 or 4 clinically significant nausea, vomiting, or diarrhoea in the presence of maximal supportive care, a required interruption of treatment  $> 2$  weeks due to toxicity. If the toxicity fails to resolve to  $\leq$  grade 2 with 14 days off treatment, the patient will be removed from the study.

No formal sample size calculation was done. Sample size will range from 6 to 19 patients.

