### **1.3.5.1    *Monotherapy***

Overall in Study SGI-110-01 (SGI-110 monotherapy in treatment-naïve and relapsed/refractory AML/MDS subjects [N=357]), the AEs with highest incidence were injection site AEs (48.2%), febrile neutropenia (47.1%), diarrhea (38.7%), thrombocytopenia (37.3%), anemia (36.1%), fatigue (35.6%), and nausea (34.2%). The related AEs with the highest incidence in this study were injection site AEs (47.1%), thrombocytopenia (28.3%), anemia (26.1%), and neutropenia (25.2%). Bone marrow suppression appears to be a consequence of the underlying disease (AML/MDS) combined with a myelosuppressive effect of SGI-110 treatment. In Study SGI-110-01 (N=357 AML/MDS subjects) other notable reported AEs included febrile neutropenia, pneumonia, and mucositis/stomatitis.

In SGI-110-03 (SGI-110 monotherapy in subjects [N=47] with advanced HCC), the AEs with the highest incidence (Stage 1 and Stage 2 combined) were neutropenia (78.7%), injection site AEs (48.9%), thrombocytopenia (40.4%), fatigue (38.3%), and leukopenia (36.2%) (Clinical Database: Table 14.6.4 and Table 14.6.14). The related AEs with the highest incidence in this study included neutropenia (74.5%), injection site AEs (48.9%), leukopenia (36.2%). In this study the SGI-110 was administered in 28 day cycles as a single agent and the safe dose was found to be 45 mg/m^2.

SGI-110 has been explored in a variety of doses and schedules. Little data exists for cycles less than 28 days; however, as ipilimumab is approved for 4 administrations every three weeks this protocol is exploring a three-week cycle of SGI-110. Recovery of myelosuppression is of substantial interest and will likely determine the safe dose. Ipilimumab has no myelosuppressive qualities and the toxicity of SGI-110 will determine its dose in all likelihood.

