### ***4.1.3 Safety Assessment***

#### ***Safety Monitoring Committee***

A Safety Monitoring Committee (SMC) will be established for the trial.

The SMC will monitor subjects' safety and will review all reported adverse events (AEs) and serious adverse events (SAEs) on an ongoing basis throughout the trial. Information on all SAEs and potential dose-limiting toxicities (DLTs) will be sent to the SMC by the end of the business day on which documented information on SAEs or DLTs was received. Enrollment of subjects into a respective cohort will be paused when the first 3 subjects have entered the first treatment cycle. A full safety data set (all AEs including SAEs, laboratory safety data, vital signs and available pharmacokinetic and pharmacodynamic data) from at least the first 3 weeks (i.e., up to Day 22, until the second cycle of SGI-110 dosing) will be submitted to the SMC.

The SMC will decide, by consensus, on DLTs relevant for the respective combination treatment, and will decide, by consensus, on dose and schedule escalation, dose and schedule de-escalation, dose and schedule expansion, suspension of enrolment, and declaration of the maximum tolerated dose (MTD) for the respective combination treatment.

DLTs are defined in Section 5.3. The process by which the MTD will be defined is described in Section 5.2.2

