## **5.3 Dose-limiting Toxicity**

DLT is defined as any of the following events occurring during the first treatment cycle and clearly related to study treatment: grade 4 neutropenia (absolute granulocyte count < 0.5 x 10^9/L, ≥ 5 days), febrile neutropenia grade ≥ 3 (absolute granulocyte count < 1.0 x 10^9/L and fever ≥ 38.5° C), platelet count < 25.000/L or thrombocytopenic bleeding, AST or ALT grade ≥ 3 for 7 days, any grade 3 or 4 non-hematologic toxicity (excluding alopecia, non pre-medicated nausea and vomiting), grade 3 or 4 clinically

significant nausea, vomiting, or diarrhoea in the presence of maximal supportive care, a required interruption of treatment > 2 weeks due to toxicity. If the toxicity fails to resolve to  $\leq$  grade 2 with 14 days off treatment, the patient will be removed from the study.

Inability to initiate Cycle 2 within 2 weeks of scheduled treatment due to slow recovery from study drug-induced toxicities and failure to meet re-treatment criteria.

The DLT observation period is defined as the first 3 weeks of treatment, i.e., from Day 1 to Day 21 of Cycle 1. Once the MTD is reached in each group, the safety data will be analysed.

Note: All AEs (including those occurring after the end of the DLT observation period) will be considered for decision-making by the SMC.

**Tolerability** will be defined as the ability to continue treatment for at least 2 cycles in a row without development of DLTs.

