## **7.2 Dose-limiting Toxicities**

Dose-limiting toxicities are defined in Section 5.3.

All presumed DLTs (as defined in Section 5.3) must be recorded immediately, i.e., within a maximum of 24 hours after becoming aware of the event, in the eCRF irrespective of seriousness and the event must be specified as a DLT. In addition, serious DLTs must be reported in an expedited manner according to the procedure for SAEs, as outlined above. Unless an NCI-CTCAE Grade 4 hematologic or a Grade 3/4 non-hematologic toxicity that occurs during the DLT observation period is clearly due to a non-drug cause, the Investigator should consider all AEs seen during the DLT observation period (from Day 1 to Day 21 of Cycle 1) to be at least possibly related to the trial treatment. In addition, the methods described in Section 6.3.5 and 7.4 should be used to assess all AEs throughout the trial until after completion of the SFU Visit(s).

Section 4.1.3 outlines the responsibilities of the SMC with respect to DLTs.

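### Section 5.3 lists a DLT (Cycle 2 not started within two weeks) that cannot be met before about Day 36, but the DLT window closes on Day 21 and no rule makes the SMC wait for the event or count it

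*Combined protocol and SAP*

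**What the plan says.** Section 5.3 sets the window: "The DLT observation period is defined as the first 3 weeks of treatment, i.e., from Day 1 to Day 21 of Cycle 1". Section 7.2 uses the same limits when it tells the investigator how to attribute "all AEs seen during the DLT observation period (from Day 1 to Day 21 of Cycle 1".

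Under the same heading, after the main DLT list, Section 5.3 adds: "Inability to initiate Cycle 2 within 2 weeks of scheduled treatment due to slow recovery from study drug-induced toxicities". The main list, in 5.3 and in the synopsis, also includes treatment interruptions of more than two weeks due to toxicity (synopsis: "in the presence of maximal supportive care, a required interruption of treatment"). The synopsis list omits the Cycle 2 item.

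Section 5.2.1 gives SGI-110 at Weeks 0, 3, 6 and 9. Section 4.1.3 pauses enrolment into a cohort after three subjects and sends the SMC safety data "from at least the first 3 weeks (i.e., up to Day 22, until the second cycle of SGI-110 dosing".

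Section 5.2.2 drives escalation and the MTD by DLT counts: no DLT in three leads to escalation, one in three leads to three more subjects, and the MTD is the highest level with no more than one DLT in six. It also lets non-DLT toxicity inform escalation. A note in 5.3 adds: "All AEs (including those occurring after the end of the DLT observation period) will be considered for decision-making by the SMC".

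**The concern.** A DLT criterion and the period for observing DLTs should fit together. Here one listed criterion can only be met after the period has ended. Nothing in the plan says whether such an event enters the 0/3, 1/3 or 1/6 count, whether the SMC must wait for it, or what happens if it is declared after escalation. Section 8.3.1 bases the MTD on a DLT-evaluable population, but Section 8.2 does not define one, so no population rule settles the matter.

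The MTD is the primary endpoint, and the remaining subjects, up to 19 in all, are treated at it. The toxicity concerned is central to the trial. Section 1.3.5.1 says that little is known about cycles shorter than 28 days and that "Recovery of myelosuppression is of substantial interest and will likely determine the safe dose". A level could be cleared while one of its subjects is still waiting for counts to recover, and the next subjects could then be dosed 15 mg/m² per day higher.

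Slow recovery can occur without a DLT inside the window. Grade 4 neutropenia lasting under five days is not a DLT (5.3). Section 5.3.1 nevertheless generally holds SGI-110 after Grade 4 haematological toxicity until eligibility levels return, which for ANC means at least 2000/µL (4.2.1).

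**Working it through.** **Timing.** Day 1 is the first SGI-110 dose, at Week 0.

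- Window end: 3 × 7 = Day 21. This reproduces 5.3 and 7.2.
- Cycle 2 due at Week 3: 1 + 21 = Day 22. This reproduces 4.1.3.
- Last permitted Cycle 2 start: 22 + 14 = Day 36.
- With the ±3-day treatment visit window in Table 6.1: 22 − 3 + 14 = Day 33, to 22 + 3 + 14 = Day 39.
- Gap to the window end: 36 − 21 = 15 days. Gap to the SMC minimum data: 36 − 22 = 14 days.

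An interruption of more than two weeks matures no earlier when the held dose is Cycle 2, so the synopsis list has the same difficulty even without the Cycle 2 item.

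**Who is exposed at planned accrual.** Section 4.1.6 assumes uniform accrual over 24 months, and the maximum is 19 subjects. With 30.44 days per month, spacing is 24 × 30.44 / 19 ≈ 38 days. When the third subject of a trio reaches Day 22, the second is at about Day 22 + 38 = 60. The next subject would start at about the third subject's Day 1 + 38 = 39. So at planned accrual the last late outcome would normally be known before anyone is dosed at the next level. The exposed case is enrolment that is clustered, or queued behind the pause. If three subjects start within two weeks, all three can be short of Day 36 when the third reaches Day 22.

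**Illustration for the clustered case only.** The documents give no rates, so both inputs are assumptions. Let w = 0.10 be the in-window DLT rate, q the further rate of slow-recovery DLTs in subjects without an in-window DLT, and p = w + q. A level is cleared by 0/3, or by 1/3 followed by 0/3.

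- All events counted: (1 − p)³ + 3p(1 − p)⁵.
- Late events of the deciding trio not counted, those of the first trio known by the second decision: (1 − w)³ + 3w(1 − p)²(1 − w)³.

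| q | All counted | Deciding trio's late events missed | Difference |
|---|---|---|---|
| 0.05 | 0.614 + 0.200 = 0.814 | 0.729 + 0.158 = 0.887 | 7 points |
| 0.10 | 0.512 + 0.197 = 0.709 | 0.729 + 0.140 = 0.869 | 16 points |

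The calculation supposes a decision at Day 22 that gives no weight to a visibly held subject and is never revisited. It shows direction, not an estimate.

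**The case against.** The SMC has wide discretion. Day 22 is a data minimum, and the reference to the second cycle of dosing could be read as actual dosing. The SMC reviews events continuously, decides by consensus what is a DLT, and can suspend enrolment or de-escalate. Counts are due before Cycle 2, so a held subject is visible at the data cut. Late events are to be considered, and non-DLT toxicity informs escalation. One can also argue that the toxicity arises in Cycle 1, and that a specific listed criterion should override a general window.

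Most of this stands as mitigation, but it does not supply a rule. The data cut is explicitly glossed as Day 22, considering an event is not the same as counting it, and the 3+3 runs on counts. A reasonable SMC could go either way under the present text.

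The objection to the size of the effect also stands. A reader might extend the table to q = 0.20 or 0.30 and report differences of 34 to 50 points. The documents give no basis for such rates. Many subjects who recover slowly would already have an in-window haematological DLT. Section 5.3.1 allows redosing at the same level, once counts recover, after uncomplicated Grade 4 toxicity of up to a week, and 5.4.2 allows G-CSF from Cycle 1. A reader might also infer a loss at planned accrual, but that needs a Day 22 decision that is never revisited, because the next subject would start at about Day 39.

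The definition of tolerability as "the ability to continue treatment for at least 2 cycles in a row without development of DLTs" fits poorly with a one-cycle window. It is not an escalation criterion, so little turns on it.

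**Conclusion.** The inconsistency is real and lies in the text itself. A listed DLT matures at about Day 36 (33 to 39), 15 days after the DLT window closes and 14 days after the SMC's minimum data. Taken literally, the window excludes it from the count that determines the primary endpoint. SMC discretion reduces the risk but requires neither waiting nor counting.

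The size of the risk cannot be derived from the documents. It depends on how often slow recovery occurs without an in-window DLT and on how closely subjects are enrolled. Exposure is mainly in clustered or queued enrolment. The 7 and 16 points above rest on assumed rates and on no SMC judgement being exercised. A reader might infer that the MTD will be biased upward, but the documents do not show that. They support only that a level could be cleared too readily in some enrolment patterns. The change should be made because it is specific, protects later subjects and costs little.

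**What to change.** 1. In 5.3 and 7.2, for a subject whose Cycle 2 is held for toxicity, extend the DLT period until Cycle 2 starts or Day 36 passes, whichever is first. State that the slow-recovery event counts as a DLT in the 3+3.
2. Add the same item to the synopsis DLT list.
3. In 4.1.3, make no escalation, expansion or MTD decision while any subject in the cohort has Cycle 2 held for toxicity and has not yet passed Day 36. State that a subject who stops before Cycle 2 for reasons other than toxicity does not hold the cohort.

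The cost is up to about two weeks for a cohort with a held subject. Table 6.1 has blood counts at Weeks 3, 4 and 6 but not Week 5. Section 6.3.7.2 already requires extra draws while a haematological event recovers, so no new scheduled visit is needed.

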### ***5.3.1 Dose Modifications***

During dose escalation, the dose of SGI-110 to be administered is determined by the dose level and the subject's body weight at consent. Thereafter, it will be determined by the MTD and the subject's body weight. Once a dose of SGI-110 is established, it should be maintained unless the subject's body weight decreases by 10% or a safety issue requires dose reduction. If a myelosuppressive DLT occurs, the patient may resume at the next lower dose level of SGI-110 after recovery of counts.

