**Dose and Schedule:**

Phase 1b, Dose Escalation: 3+3 dose escalation.

SGI-110: start at 30 mg/m^2 s.c.day (Dose Level +1) on W0, 3, 6, 9 Day 1 - 5 q21 days. Dose Level -1): 15 mg/m^2 day; Dose Level +1: 45 mg/m^2 day; Dose Level +2: 60 mg/m^2 day.

Ipilimumab: 3 mg/Kg i.v. over 90 minutes on W1, 4, 7 and 10 for a total of 4 cycles.

During dose escalation, subjects will be allocated to 1 of 3 dose levels of SGI-110 in combination with ipilimumab 3 mg/Kg according to a classical, dose-escalation 3 + 3 design (see Figure 1). Treatment within the 4 SGI-110 Dose Levels will proceed in sequence provided there are no DLTs (see Section 5.3). Details of this evaluation and the thresholds for toxicity and dose escalation are described fully in Sections 5.3.

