### **SGI-110**

SGI-110 should be reconstituted under aseptic conditions and kept under refrigerated conditions.

Drug product is available as a two-vial system, referred to as (1) SGI-110 for Injection, 100 mg and (2) SGI-110 Diluent for Reconstitution, 3 mL:

- SGI-110 for Injection, 100 mg contains SGI-110, 100 mg of free acid equivalent, as a dry powder lyophile.
- SGI-110 Diluent for Reconstitution, 3 mL contains 3 mL of a non-aqueous diluent for reconstitution.

SGI-110 for Injection, 100 mg vial is stored at 2°C to 8°C in the original packaging until use. SGI-110 Diluent for Reconstitution, 3 mL can be stored at 2°C to 30°C in an upright position until use. Both vials are preservative free and for single use only.

The diluent is comprised of 3 commonly used excipients, propylene glycol, glycerin, and ethanol, that are generally recognized as safe (GRAS). All 3 excipients are pharmaceutically acceptable solvents previously used in drug products approved for SC administration. SGI-110 solution is reconstituted at a maximum concentration of 100 mg/mL for SC administration. Both product and diluent are contained in clear glass vials stoppered with a latex-free rubber stopper and capped with an aluminum flip-off seal. The reconstituted SGI-110 solution is chemically stable for 8 days under refrigerated conditions; however, there are no preservatives in the custom diluent or lyophilized vials. For study centers using the PhaSeal® system for reconstitution of SGI-110, it is recommended to use the Assembly Fixture provided by the manufacturer to attach the PhaSeal® Protector to the SGI-110 lyophilized vial and custom diluent vial, and to filter the final reconstituted product with a 0.2 micron filter. This is to eliminate the presence of foreign material resulting from stopper coring in the final dispensed product.

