## **5.2 Method of Assigning Subjects to a Treatment**

After informed consent has been obtained, the patient will be enrolled into the study by a dedicated software, that will be available to the participant Center, and obtain a patient number. The exact procedures for using the dedicated software will be detailed in a separate document.

Following completion of all Screening Phase evaluation, and checking inclusion criteria site personnel will register the patient to obtain a treatment assignment (STEP2). The e-Clinical system assigns subjects to the SGI-110 dose level.

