### ***5.2.1 Dosage and Administration***

#### ***SGI-110 schedule***

SGI-110 will be administered:

Start at 30 mg/m^2 day s.c. on W0, 3, 6, 9 Day 1 - 5 q21 days. Dose Level -1: 15 mg/m^2 day; dose level +1: 45 mg/m^2 day, Dose Level +2: 60 mg/m^2 day for a total of 4 cycles.

SGI-110 is administered by SC injection preferably in the abdominal area; however the thigh and arms may be used. A Luer-Lok disposable syringe should be used when dispensing and administering SGI-110. Due to the slightly viscous nature of the preparation, use of thin-walled subcutaneous needle is highly recommended for ease of subcutaneous administration and subject comfort. SGI-110 should be injected slowly (up to one minute) as some injection site discomfort or pain may be experienced.

If injection site pain is reported upon injection, apply ice packs to the injection site both before and after injection. If the injection site events are reported at subsequent injections despite slow injection and the use of ice packs, pre-treatment with topical or systemic analgesics can be considered. The total amount (in mg) of SGI-110 to be administered will be determined based on the body surface area (BSA). In calculating the BSA, actual heights and weights taken at enrolment should be used. There will be no adjustments to “ideal” body weight or dose modifications related to changes in body weight < +/- 10%. The institutional standard for calculating BSA is acceptable.

The site(s) of SGI-110 SC injections will be captured on the dosing CRF.

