### ***6.3.1 Medical History, Physical Exam, Physical Measurements***

A detailed Medical History will be obtained at Screening. Medical history must include date of diagnosis, including histological or cytological documentation of malignancy. Any toxicity related to previous treatments should be mentioned, if applicable.

A complete physical examination including subject's height and weight will be performed at Screening. Prior to dosing (within 3 days), the subject's weight must be obtained to calculate the ipilimumab dose and the subject's body surface area on which SGI-110 dose is calculated.

If the Screening physical exam is conducted within 24 hours of dosing on Week 0, then a single examination may count as both Screening and Pre-dose examination. Subsequent physical exams will be performed if clinically indicated. Any physical examination finding that qualifies as an AE or SAE must be documented on the appropriate CRF pages. Pre-treatment events present within 2 weeks of starting therapy, whether or not related to current disease, will be captured prior to the study start. Any worsening ( $\geq 1$  Grade from Baseline) will be documented as an AE in the CRF.

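### The cohort table in 4.1.4 gives all four SGI-110 levels in mg/kg, while the dosing sections use mg/m²; one synopsis entry also labels the 30 mg/m² start Dose Level +1

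*Combined protocol and SAP*

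**What the plan says.** **Unit.** The study schema table in 4.1.4 prints mg/kg in all four SGI-110 rows: 15, 30, 45 and 60. The ipilimumab column beside it is also in mg/kg, which is correct for that drug. The synopsis and sections 4.1.1, 5.2.1, 5.2.2 and 8.1 give SGI-110 as 15, 30, 45 and 60 mg/m² per day. Section 5.2.1 says that the total mg amount "will be determined based on the body surface area (BSA"), and 6.3.1 also treats BSA as the basis for the SGI-110 dose.

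**Label.** The synopsis Dose and Schedule entry gives the 30 mg/m² start as "s.c.day (Dose Level +1) on W0, 3, 6, 9 Day 1 - 5 q21 days". The same entry then gives Dose Level +1 as 45 mg/m². Wherever else the 30 mg/m² dose carries a label (synopsis Study Design and Statistical Methods, 5.2.2, 8.1), it is Dose Level 0.

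**Weight.** Three sections describe the weight input differently.
- 5.2.1 uses height and weight at enrolment and rules out "dose modifications related to changes in body weight < +/- 10" percent.
- 5.3.1 says that during escalation "the dose of SGI-110 to be administered is determined by the dose level and the subject's body weight at consent". Once the dose is set, "it should be maintained unless the subject's body weight decreases by 10% or a safety issue requires dose reduction". BSA is not mentioned.
- 6.3.1 asks for a weight within 3 days before dosing, which "must be obtained to calculate the ipilimumab dose and the subject's body surface area on which SGI-110 dose is calculated".

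**Assignment.** Section 5.2 states: "The e-Clinical system assigns subjects to the SGI-110 dose level".

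**The concern.** The primary endpoint is the MTD, so the link from a level's name to a dose is part of what the trial estimates. In 4.1.4 that link carries the wrong unit in every row. Nothing inside the table reveals the error, because mg/kg is the right unit for the neighbouring column.

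A unit or label mistake would act on the first Cycle 1 dose, inside the Day 1 to 21 DLT window. This is the first trial of the combination, the drug is myelosuppressive, and the 21-day cycle is shorter than the usual 28 days.

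The label matters separately. Escalation decisions, safety reports and the 5.3.1 provision for restarting one level down after a myelosuppressive DLT all use level names. Under the synopsis entry, Level +1 could mean 30 or 45 mg/m². The step between those doses is not trivial on the protocol's own record. Section 1.3.5.1 reports 45 mg/m² as the safe single-agent dose in hepatocellular carcinoma on 28-day cycles. Section 1.3.5.2 reports that de-escalation to 30 mg/m² was needed with carboplatin.

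**Working it through.** **1. Which unit fits the protocol's own justification.** Section 1.5 puts the starting dose at 33% of the single-agent MTD. Section 1.3.2 gives that MTD as 90 mg/m² per day in MDS. Then 30 / 90 = 33%, so the stated figure is reproduced in mg/m². It has no such meaning for 30 mg/kg.

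**2. Size of the unit conflict.** The documents give no body sizes and 5.2.1 leaves the BSA formula to the institution, so both are assumptions here. I use BSA = √(height in cm × weight in kg / 3600).
- Intended daily dose = level × BSA.
- Literal 4.1.4 dose = level × weight.
- Ratio = weight / BSA. The level cancels, so the ratio is the same in all four rows.

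| Assumed patient | BSA (m²) | Level 0 at 30 mg/m² | Level 0 at 30 mg/kg | Ratio |
|---|---|---|---|---|
| 50 kg, 155 cm | 1.467 | 44.0 mg | 1,500 mg | 34.1 |
| 70 kg, 170 cm | 1.818 | 54.5 mg | 2,100 mg | 38.5 |
| 100 kg, 185 cm | 2.267 | 68.0 mg | 3,000 mg | 44.1 |

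**3. Would it be noticed?** Section 5.1.4 gives 100 mg vials and says "SGI-110 solution is reconstituted at a maximum concentration of 100 mg/mL for SC administration". For the 70 kg patient:
- mg/kg reading: 2,100 / 100 = 21 vials, and at least 21 mL by subcutaneous injection each day.
- mg/m² reading: 54.5 mg, which is less than one vial and about 0.5 mL.

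A pharmacy would probably query the first.

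**4. Size of the label conflict.** 45 / 30 = 1.50, a 50% difference. For the 70 kg patient, 45 × 1.818 = 81.8 mg, still within one 100 mg vial. The vial count that would expose the unit error would not expose this one.

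**5. Size of the weight-rule conflict.** At fixed height, BSA varies with the square root of weight, so the mg dose changes by √(weight ratio) − 1.
- 5% loss: √0.95 − 1 = −2.5%
- 10% loss: √0.90 − 1 = −5.1%
- 10% gain: √1.10 − 1 = +4.9%
- 15% loss: √0.85 − 1 = −7.8%
- 15% gain: √1.15 − 1 = +7.2%

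These differences arise mainly from Cycle 2, after the DLT window, so they have little effect on the MTD.

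**The case against.** The strongest reply is that no one could doubt the intended unit. The doses are in mg/m² throughout the synopsis, in 1.5, 4.1.1, 4.1.5, 5.2.1, 5.2.2 and 8.1, and full level lists in mg/m² stand in the synopsis, 5.2.2 and 8.1. The mg/kg in 4.1.4 is almost certainly copied from the ipilimumab column. The label slip largely corrects itself, because 30 mg/m² is printed immediately before it and Level 0 is the only name left for that dose. All of this stands. It bears on how likely a mistake is, and does not remove a wrong unit and a wrong label from the current text.

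Some stronger readings are tempting but go beyond the documents.
- **That 5.3.1 is a second instruction to dose per kg.** It gives no unit. BSA is computed from weight, so the sentence can be loose wording for BSA dosing. Only 4.1.4 firmly contradicts 5.2.1.
- **That the site receives nothing but a level and must convert it from the 4.1.4 table.** Section 5.2 says that the system assigns the level. It does not say what else the system displays, and it leaves the software procedures to a separate document. Correct level lists also stand elsewhere, and Figure 1 is not available to check.
- **That patients face a dose many times the known MTD.** Setting the literal per-kg dose against 90 mg/m² sizes an event that the vial count and injection volume would probably stop.

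**Conclusion.** The plan is wrong as written in two operative places: the SGI-110 unit in the 4.1.4 table and the level label in the synopsis Dose and Schedule entry. Both should be corrected in the next amendment.

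Read literally, the table gives about 34 to 44 times the intended dose. That range rests on assumed patients of 50 to 100 kg and the BSA formula shown above. It measures how far apart the two texts are and is not a forecast of overdosing. The label conflict is worth 50% of dose if the label is followed instead of the number beside it. The differences over which weight to use, and over whether a gain of 10% or more changes the dose, are real but minor, at about 2.5% to 8% of dose for weight changes of 5% to 15%.

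A reader might infer that the design itself is compromised. The documents do not support that: the sample size range, the DLT definition, the escalation rule and the analyses are the same whichever way these entries are read, once mg/m² is applied.

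**What to change.** - **4.1.4:** change the SGI-110 column to 15, 30, 45 and 60 mg/m²/day.
- **Synopsis, Dose and Schedule:** change the label after 30 mg/m² from Dose Level +1 to Dose Level 0.
- **5.2.1:** state one rule. The mg dose is the level in mg/m² times the BSA from enrolment height and weight, re-calculated only when weight differs from enrolment by 10% or more in either direction.
- **5.3.1:** replace the body-weight wording with a reference to 5.2.1, keeping the provision for safety reductions.
- **6.3.1:** refer to 5.2.1, and say that the pre-dose weight serves for the ipilimumab mg/kg dose and to check the 10% threshold.

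The cost is one table column, one label and wording in three sections. No new data are needed, because height is taken at Screening and weight and BSA before dosing are already in the schedule in 6.1.
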